#### Quality of life

Quality of life will be measured using the EQ-5D questionnaire at 90 days.

#### Cost data

A cost-effectiveness analysis will form a component of the future RCT. During the pilot phase, 90-day cost data will be gathered to develop this analysis, including:

• Drug usage

• Investigations

• Hospital admissions

• Outpatient admissions

• GP contacts

#### Process of care measures

The process of care measures are the patient’s blood pressure at 90 days and serum cholesterol at 90 days. Persistence with treatment at first specialist appointment and persistence with treatment at 90 days will be recorded.

### Additional outcome measures for the pilot randomised control trial

#### Recruitment rate

• Number assessed for eligibility by site (emergency department, out-of-hours general practice or general practice).

• Number recruited into the pilot RCT by site.

• Number who received the allocated intervention by site (including the nature of receipt of intervention group medications in the control group).

• Number followed up at 90 days by site.

• Basic demographic data and data on the presentation of the patient to the site will be collected on patients excluded or missed from the study by each site to help determine the feasibility of the trial.

• TIA clinics in participating hospitals will be audited to cross-check the data collected from each site and diagnoses of patients from participating practices will be obtained.

#### Sample size calculation

The proportion of patients experiencing a stroke within 90 days by allocation will be used to assist the sample size calculation for the future RCT. Side effects, tolerability and quality of life will be assessed from the reasons given by patients for omitting or stopping medication and their responses to the standard side-effect questionnaire at 90 days.

#### Outcome measures for the diagnostic accuracy study

• Clinic’s diagnosis of TIA or minor stroke compared with the primary care physician’s diagnosis of possible or probable TIA and with the primary care physician’s ABCD2 score.

• Clinic-defined ABCD2 score compared with primary care physician’s ABCD2 score.

• Features recognised by primary care physicians that predict TIA.

• Clinical features recognised by primary care physicians but not by specialists and vice versa.

• How well the clinical features and ABCD2 score predict for anterior versus posterior circulation events.

### Follow-up

There will be a 90-day follow-up clinic at the hospital. This will be supplemented by a review of GP and hospital records, flagging with the NHS Central Register and telephone contact or home visits for patients who do not or cannot attend the 90-day follow-up clinic. These follow-up mechanisms will:

• Confirm the final diagnosis.

• Record the patient’s blood pressure and serum cholesterol at 90 days.

• Identify primary and secondary outcomes.

• Monitor for serious adverse events and deaths.

• Record any changes in treatment and persistence with medication at 90 days.

• Collate cost data.

• Assess the patient’s quality of life at 90 days.

• Record side effects.

Prior to contacting participants for a follow-up, their health status will be established via their GPs to establish that they are not deceased and to ascertain whether their mental capacity has been lost. Participants identified as having lost capacity will be contacted and an appropriate consultee appointed. Detailed information about the trial will be provided to the consultee, and if in agreement an appointment will be made for the participant’s follow-up visit, at which the consultee must be present and must sign a declaration form to confirm their accordance.

Blood pressure and serum cholesterol readings taken at the 90-day follow-up clinic will be sent to the patients’ GP.

Where strokes are identified, anonymised copies of the relevant clinical information (from GP and hospital records, post-mortem reports, scan reports and so on) will be obtained and sent to an independent end-point committee, who will be blinded to treatment allocation. Independently of each other, the end-point committee will determine whether or not a stroke occurred, and if so, what sort of a stroke it was. Characterisation will include: ischaemic or haemorrhagic and disabling, non-disabling or TIA. Secondary outcomes will also include all vascular events, all major bleeding and deaths. Relevant clinical records will be scrutinised by an independent expert blinded to treatment allocation, who will determine whether or not a vascular event or major bleeding occurred, and what it was using standard case definitions. All hospital admissions will be scrutinised for possible adverse events and the clinical records sent to an independent expert for review.

We will follow up all patients, including those in the RCT and the diagnostic study.

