## Methods/Design

### Outline of design

A pilot trial will recruit patients with symptoms suggestive of TIA or minor stroke in general practices from the catchment of three hospital TIA clinics (Birmingham, Cambridge and Oxford) and the emergency department in Cambridge (Figure 1). Embedded within this pilot trial will be a diagnostic accuracy study comparing the initial diagnosis made by the primary care physician with the final diagnosis following review and investigation at the specialist clinic. When a primary care physician sees a patient with a history suggestive of TIA, are cord will be made of whether TIA or a minor stroke is probable or possible. All patients will then be referred to the TIA clinic. Probable cases will be invited by the primary care physician to enter the trial and the diagnostic accuracy study; possible cases will be invited to enter the diagnostic accuracy study only. Patients will be allocated by telephone to additional pre-TIA clinic drug treatment and usual care or usual care only, with allocation by a minimisation scheme using the following categories: TIA clinic catchment area, primary care clinic type and ABCD2 score. The TIA clinic will record the final diagnosis and adjust treatment accordingly. ‘Usual care’ implies initiation of aspirin therapy and referral to the specialist TIA clinic. The primary outcome will be the number of strokes at 90 days. Semi-structured interviews will be undertaken with the aim of determining how trial procedures might be modified for the main trial.

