#### Initial presentation in daytime general practice

Participating general practices have a lead GP, who coordinates recruitment into the trial. Patients may present with suspected TIA at any time to a GP in the practice, who may be assisted in aspects of patient care by a practice nurse. When a patient presents, the clinician will take a history, examine the patient and come to an initial diagnosis of possible or probable TIA or minor stroke as per usual practice, and then:

1. Inform the patient of the suspected diagnosis as per usual practice.

2. Discuss the information sheet with the patient.

3. Confirm the inclusion and exclusion criteria.

The patient will be given time to consider the information and to ask questions. The clinician will then:

4. Obtain informed consent if the patient is willing to take part.

5. Record clinical features and whether TIA is probable or possible.

For patients diagnosed with probable TIA or minor stroke, the clinician will also undertake the following:

6. Consider the relative indications and contraindications to therapy.

7. Take the patient’s blood pressure.

8. Record any current medication.

9. Randomise the patient to the intervention or control arm.

10. Prescribe and dispense the allocated medication.

11. Ask the patient to bring their medication to the specialist clinic.

Finally, all patients will be referred to the TIA clinic with urgency determined by local guidelines. The GP will also arrange any additional appropriate follow-up consistent with usual practice.

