#### Specialist clinic

All patients will have been referred to the TIA clinic as per local protocol consistent with NICE guidelines and therefore will usually be reviewed within 7 days of symptom onset (or within 24 hours for higher risk TIAs). Specialists will manage patients according to their usual practice, including changing any medication started by the primary care physician. In addition, the specialist doctor, supported by nursing staff, willrecord clinical features, ABCD2 score, blood pressure, final diagnosis, current medication, persistence with primary care initiated medication and changes to medication.

Additionally, the research nurse will check the patient’s hospital record for a final diagnosis when this is available if it is not confirmed during the initial TIA clinic attendance; the research nurse will also obtain an up-to-date medication list from the patient’s GP record if this has not been provided at initial presentation.

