### Analysis

For the statistical analysis,baseline, TIA clinic and follow-up variables will be summarised by treatment group and overall. Categorical variables will be summarised by the number and percentage of subjects in each category. Continuous variables will be summarised using the mean, median, standard deviation, interquartile range and minimum and maximum values. For the main trial, logistic regression analysis of the primary and secondary outcomes will determine the efficacy of rapid drug treatment initiation after adjusting for the variables for catchment area, clinic type and ABCD2 score. Analysis will be according to the intention-to-treat principle and the treatment effect will be expressed as an odds ratio and its corresponding 95% confidence interval. The influence of missing data on the robustness of the findings will be explored in sensitivity analyses (replacement by last value, mean of series and multiple imputation). All statistical analyses will be pre-specified in a comprehensive statistical analysis plan, which will be agreed by the trial steering committee in advance of the final database lock.

Clinical outcomes will also be analysed according to the following sub-groups:

• Specialist diagnosis of non-TIA, TIA or stroke.

• Primary care physician’s diagnosis of possible or probable TIA.

• Specialist’s ABCD2 score.

• Primary care physician’s ABCD2 score (both as recorded by the minimisation hotline and the case report forms).

• Baseline therapy.

• Recruitment site by location (Birmingham, Cambridge or Oxford) and clinic type (out-of-hours general practice, daytime general practice or emergency department).

• First TIA or stroke versus recurrent TIA or stroke.

We will analyse the TIA versus minor stroke outcome rates in both RCT groups to exclude diagnostic bias.

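### Only events already identified as strokes are stated to reach the blinded committee, and the planned TIA-versus-stroke comparison cannot rule out biased labelling

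*Protocol article*

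**What the plan says.** All references are to the protocol article.

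- **Comparison.** Outline of design allocates patients to "additional pre-TIA clinic drug treatment and usual care or usual care only". No placebo and no masking of patients or clinicians is described. The term open-label is not used.
- **Visibility of allocation.** The steps at initial presentation include "Ask the patient to bring their medication to the specialist clinic". Under Specialist clinic, the specialist records "persistence with primary care initiated medication and changes to medication".
- **Outcome.** "The primary outcome will be the number of strokes at 90 days" (Outline of design). The Outcome measures section places this among the measures for the future trial.
- **Route to blinded review.** Follow-up states: "Where strokes are identified, anonymised copies of the relevant clinical information (from GP and hospital records" and other sources) are obtained and sent to an independent end-point committee that is blinded to allocation. The committee decides whether a stroke occurred and of what kind: "Characterisation will include: ischaemic or haemorrhagic and disabling, non-disabling or TIA".
- **Other review.** The same section turns to secondary outcomes and adds: "Relevant clinical records will be scrutinised by an independent expert blinded to treatment allocation". This expert decides whether a vascular event or major bleed took place and what it was. Every hospital admission is also examined for possible adverse events, with expert review.
- **Check for bias.** The Analysis section ends: "We will analyse the TIA versus minor stroke outcome rates in both RCT groups to exclude diagnostic bias".

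**The concern.** The line between a TIA and a minor stroke is a matter of judgement. The article's definition of TIA relies on imaging to show absence of infarction only where imaging is available. If those who first name an event know that the patient was given extra preventive drugs, mild events could be named differently in the two arms.

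Blinded adjudication guards against this only if it sees events on both sides of the line. Here the stated trigger is that a stroke has already been identified. An over-called stroke can be corrected. An under-called stroke has no stated route to correction. If under-calling were more common in one arm, it would lower that arm's stroke count.

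The comparison in the Analysis section is offered as the safeguard. If it cannot do that job, an unremarkable result could be taken as clearing a bias it did not test.

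**Working it through.** **Reading the text**

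1. *Who can know the allocation.* The comparison is added drugs against none, patients bring their medication to the clinic, and the specialist records it. That treatment is open is an inference, but a secure one.
2. *What the committee can change.* The way in is an identified stroke. The results include stroke of several kinds, or TIA. Stroke to TIA is therefore possible; for TIA to stroke, no way in is stated.
3. *Whether another route closes the gap.* The blinded expert's task is set out with secondary outcomes, and the admissions review is for adverse events. Neither is said to pass cases to the committee or to change the stroke count. The Background also reports guidance that suspected TIA or minor stroke should not routinely be admitted, so an admissions screen can miss mild events.

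**Whether the check can work at any sample size**

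Let the true control-arm rates be 10% for stroke (the upper figure of the Background's illustrative fall from 10% to 2%) and t for TIA. Let f be a fraction of intervention-arm strokes.

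- Treatment does nothing, and f of the strokes are labelled TIA: observed stroke rate 0.10(1 − f), observed TIA rate t + 0.10f.
- Labelling is perfect, and treatment turns f of the strokes into TIAs: the same two rates.

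The expected counts are identical, so no test on them can tell the two apart. Equal rates do not clear bias either, because a labelling shift can cancel a true difference in the other direction.

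**Precision at pilot size**

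Inputs: 100 randomised (Recruitment section), taken as 50 per arm because no ratio is stated.

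- *Odds ratio for the split*, with an assumed 4 strokes and 4 TIAs in each arm: SE of log OR = √(1/4 + 1/4 + 1/4 + 1/4) = 1.0, so the 95% CI is exp(±1.96) = 0.14 to 7.1.
- *Power to notice mislabelling.* Assume treatment does nothing and t is 5% or 10%. All stroke/TIA/neither counts for 50 per arm were enumerated, and Fisher's exact test (two-sided 0.05) was applied to stroke against TIA by arm.

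| f (assumed) | Apparent stroke risk ratio, 1 − f | Power of the check |
|---|---|---|
| 25% | 0.75 | about 0.05 |
| 50% | 0.50 | 0.15 (t = 5%), 0.14 (t = 10%) |

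- *One relabelled event* moves an arm's rate by 1/50 = 2 percentage points.

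**If the process is carried into a main trial**

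Assume 500 per arm, no true effect, and a 10% stroke rate in both arms. The chance of a significant difference in labelled strokes is Φ[(d − 1.96·SE₀)/SE₁], where d is the apparent difference, SE₀ its standard error under a common rate and SE₁ under separate rates.

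- f = 50%: d = 0.050, SE₀ = √(2 × 0.075 × 0.925/500) = 0.01666, SE₁ = √((0.09 + 0.0475)/500) = 0.01658, giving 0.85.
- f = 25%: d = 0.025, SE₀ = 0.01787, SE₁ = 0.01785, giving 0.29.

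The article states no sample size or power for the stroke outcome, so there is no figure of its own to reproduce.

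**The case against.** Much can be said for the plan.

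- *The text does not bar TIAs from the committee.* A reader might infer that an event first called TIA can never be upgraded. The article does not say so. It states one trigger and is silent on the rest, and the listing of TIA among the committee's results could hint that TIAs are seen too. This stands as a limit on the claim. The stated trigger still does not include them.
- *There is other blinded review.* The vascular-event expert decides what an event was, and every admission is examined. For admitted patients in particular this is a real mitigation. What is missing is a stated link to the stroke outcome.
- *Packets might reveal treatment.* A reader might infer that prescribing entries in the records unblind the committee. The article says the committee is blinded. How packets are prepared is operational detail that a journal article can leave to fuller documents, so no finding is made on it.
- *This is a pilot.* The logistic regression of outcomes is for the main trial, and the pilot's stroke proportions only help to size it. The sampling error of a 10% rate in 50 patients is 1.96 × √(0.1 × 0.9/50) = 8.3 points, well above a 2-point shift from one event. This stands: it would be wrong to infer that the pilot's own conclusions are invalidated.
- *The Analysis sentence is ambiguous.* It may mean outcomes by index diagnosis. The odds-ratio calculation would then not apply, but the sentence would fare no better, since that comparison does not test how outcome events are labelled.

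**Conclusion.** The point holds in a limited form. As written, blinded adjudication of the stroke outcome has a stated way in only for events already identified as strokes, in a comparison where allocation is visible to clinicians. The other blinded reviews narrow the gap but are not said to close it. Separately, the TIA-versus-minor-stroke comparison cannot exclude diagnostic bias on either reading of the sentence. If it compares outcome events, it is also very imprecise at about 50 per arm.

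The documents do not show that mislabelling will occur, or in which direction. The mislabelling fractions, the TIA rates, the 4-and-4 split and the 500 per arm are all assumptions, and the article gives no expected number of strokes for the pilot. The consequence in the pilot is modest: a preliminary stroke rate by allocation that may be shifted by a couple of points per event. The greater stake is that the pilot tests the outcome measures for the main trial, so the referral rule would be carried forward. It should be corrected, but it is not fatal.

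**What to change.** 1. In Follow-up, widen the trigger to *where a stroke or TIA is suspected or identified*. Send all such events, and deaths of possible cerebrovascular cause, to the existing blinded committee, and state that its classification defines the stroke outcome.
2. In Analysis, replace the aim of excluding diagnostic bias with that of exploring it. Support it with a table, by arm, of local label against committee label, so that changes in both directions are visible. State whether the comparison concerns outcome events or index diagnosis.

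The cost is a small number of extra packets for a committee that already exists. The work is on records, so it needs no new patient contact although recruitment has closed.

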### Analysis

For the statistical analysis,baseline, TIA clinic and follow-up variables will be summarised by treatment group and overall. Categorical variables will be summarised by the number and percentage of subjects in each category. Continuous variables will be summarised using the mean, median, standard deviation, interquartile range and minimum and maximum values. For the main trial, logistic regression analysis of the primary and secondary outcomes will determine the efficacy of rapid drug treatment initiation after adjusting for the variables for catchment area, clinic type and ABCD2 score. Analysis will be according to the intention-to-treat principle and the treatment effect will be expressed as an odds ratio and its corresponding 95% confidence interval. The influence of missing data on the robustness of the findings will be explored in sensitivity analyses (replacement by last value, mean of series and multiple imputation). All statistical analyses will be pre-specified in a comprehensive statistical analysis plan, which will be agreed by the trial steering committee in advance of the final database lock.

Clinical outcomes will also be analysed according to the following sub-groups:

• Specialist diagnosis of non-TIA, TIA or stroke.

• Primary care physician’s diagnosis of possible or probable TIA.

• Specialist’s ABCD2 score.

• Primary care physician’s ABCD2 score (both as recorded by the minimisation hotline and the case report forms).

• Baseline therapy.

• Recruitment site by location (Birmingham, Cambridge or Oxford) and clinic type (out-of-hours general practice, daytime general practice or emergency department).

• First TIA or stroke versus recurrent TIA or stroke.

We will analyse the TIA versus minor stroke outcome rates in both RCT groups to exclude diagnostic bias.

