#### Outcome measures for the future randomised control trial

##### Primary outcome measure

The number ofstrokes within 90 days of randomisation.

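### Two of the three named missing-data analyses do not suit the stroke-within-90-days outcome, and none varies the missing-at-random assumption, so agreement among them could give false reassurance

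*Protocol article*

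**What the plan says.** The primary outcome intended for the future trial is "The number ofstrokes within 90 days of randomisation" (Primary outcome measure). The clinical secondary outcomes are also events in the same window. Under Analysis, for the main trial, "logistic regression analysis of the primary and secondary outcomes will determine the efficacy of rapid drug treatment initiation", and "the treatment effect will be expressed as an odds ratio and its corresponding 95% confidence interval". The same paragraph says the influence of missing data will be explored in "sensitivity analyses (replacement by last value, mean of series and multiple imputation". No method is tied to a type of outcome.

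The measurement schedule bears on whether those methods can work:

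- Follow-up: "There will be a 90-day follow-up clinic at the hospital". Review of GP and hospital records, flagging with the NHS Central Register, and telephone contact or home visits for non-attenders back it up.
- Quality of life: "Quality of life will be measured using the EQ-5D questionnaire at 90 days". No earlier measurement is mentioned.
- Serum cholesterol is named only at 90 days. Blood pressure is taken at presentation, at the specialist clinic and at 90 days. Persistence with treatment is recorded at the first specialist appointment and at 90 days.
- Before patients are contacted for follow-up, their GPs are asked about them "to establish that they are not deceased and to ascertain whether their mental capacity has been lost". Those who have lost capacity can be seen if a consultee agrees and is present.

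Detail is deferred: "All statistical analyses will be pre-specified in a comprehensive statistical analysis plan".

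**The concern.** A missing-data sensitivity analysis should show how far the result moves when the assumption about the unseen outcomes changes. Last value and mean of series were devised for repeated numerical measurements. A first stroke within 90 days is a single yes/no fact, so neither has a sensible meaning for it. Multiple imputation does, but as ordinarily run it assumes that, given the observed data, missing patients have the same risk as those seen.

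Death and loss of capacity can both follow a stroke, so a link between the outcome and the chance of its being unknown is plausible. If such a link exists, no listed method would show it. Three methods giving similar answers would then look like robustness without having tested it. What is at stake is how the main trial's odds ratio is read, since a few unknown outcomes matter when events are few.

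**Working it through.** The article gives no missing rate, and no sample size or power for the stroke outcome, so there is no stated figure to reproduce. The check has three parts.

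**1. What each method does to an event outcome**

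| Method | Unknown stroke status becomes | Fit |
|---|---|---|
| Last value | 0: the last known state before loss, for a patient with no event so far, is always no stroke | A fixed answer, not an estimate |
| Mean of series | Within a patient there is no series; across patients it is a fraction such as 0.06 | Not a valid 0/1 response |
| Multiple imputation | Drawn 0 or 1 from a model | Valid under missing at random |

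EQ-5D, and cholesterol as far as stated, have no earlier value. Blood pressure and persistence do, so last value can at least be computed for them.

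**2. Can the methods agree and still be wrong?**

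Inputs: risks of 10% (control) and 2% (intervention), taken from an illustration in the Background and not a design assumption; a fraction m missing in each arm (assumed 10% or 20%); control patients missing at random; missing intervention patients at k times the observed risk (assumed). Results are expected values.

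True odds ratio = (0.02/0.98) / (0.10/0.90) = 0.184.

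The observed intervention risk q solves (1−m)q + m·k·q = 0.02. Multiple imputation under missing at random compares q with 0.10. Last value compares (1−m)q with (1−m)×0.10.

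- m = 0.10, k = 1: q = 0.02. Multiple imputation 0.184; last value 0.185.
- m = 0.10, k = 3: q = 0.02/1.2 = 0.0167. Multiple imputation (0.0167/0.9833)/(0.10/0.90) = 0.153; last value (0.015/0.985)/(0.09/0.91) = 0.154.
- m = 0.20, k = 5: q = 0.02/1.8 = 0.0111. Multiple imputation 0.101; last value 0.103.

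Pooled-mean replacement moves the other way. At m = 0.10 and k = 1 the pooled observed risk is 0.06, so the arm risks become 0.9×0.10 + 0.1×0.06 = 0.096 and 0.9×0.02 + 0.1×0.06 = 0.024. The odds ratio is (0.024/0.976)/(0.096/0.904) = 0.23, although nothing is wrong with the data. At k = 3 it is 0.20.

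The result depends on the mechanism. If missing patients in both arms carry three times the observed risk (m = 0.10), the observed risks are 0.10/1.2 = 0.0833 and 0.0167. Multiple imputation then gives (0.0167/0.9833)/(0.0833/0.9167) = 0.186, almost the true value. The distortion above needs the excess risk to differ by arm.

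**3. What a range over the assumption would show**

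Assume 50 patients per arm, missing patients included, with 5 observed strokes in control and 1 in intervention. The worst case gives every missing intervention patient a stroke and no missing control patient one; the best case is the reverse.

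- 2 missing per arm: best (1/49)/(7/43) = 0.13; worst (3/47)/(5/45) = 0.57.
- 5 missing per arm: best (1/49)/(10/40) = 0.08; worst (6/44)/(5/45) = 1.23.
- The worst case reaches 1.0 at 4 missing in the intervention arm (5/50 against 5/50), which is 8% of that arm.

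None of the three listed methods reports such a range.

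**The case against.** The strongest objection is that few stroke outcomes should be unknown. A missed visit is not a missing stroke: records, the register, telephone contact and home visits are there to identify outcomes, and suspected strokes are adjudicated from documents that include post-mortem and scan reports. Patients who died or lost capacity are those these sources should find. A reader might infer from the GP status check that 90-day visits fail because of death or incapacity. The Follow-up section does not say so; it provides a consultee route by which patients without capacity can still be seen. This objection stands and limits the likely size of the problem.

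Three further points also stand in part. The logistic model is stated for the main trial, while the pilot mainly reports recruitment, follow-up, a preliminary event rate and adverse events. The missing-data sentence covers the findings in general, and last value can be computed for blood pressure and persistence. Multiple imputation, which is on the list, is a proper method for a binary outcome under missing at random.

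The last objection is that detail is left to a statistical analysis plan that is not shown. That excuses the absence of imputation-model variables or tipping-point ranges. It does not excuse the choice made here, because the article itself names the methods and two of them do not suit the outcome.

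**Conclusion.** The point holds in limited form. For stroke within 90 days and the other event outcomes, last value and mean of series are unsuitable, and they have nothing to work on for EQ-5D or, as far as stated, cholesterol. Multiple imputation is sound under missing at random, but no listed analysis departs from that assumption. Agreement among the three could therefore reassure falsely if the patients whose status stays unknown are at different risk, particularly if that difference is not the same in both arms.

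A reader might go further and infer that the listed analyses would mislead. The document does not support that. It states no missing rate, the bias above appears only under assumed mechanisms, and its direction varies: mean replacement pulls towards no effect. Nor does the article support a claim about lost confidence-interval coverage for continuous outcomes. It plans summaries for those, and its only stated interval is for the odds ratio.

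The effect on the pilot's descriptive feasibility results is small and cannot be sized from the document. The odds ratios in the working rest on the Background's 10% and 2%, equal arms, and assumed missing rates and risk multipliers.

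**What to change.** Change the missing-data sentence under Analysis, and carry the change into the statistical analysis plan:

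- Drop last-value and mean-of-series replacement for event outcomes and for measures taken only at 90 days.
- Keep multiple imputation, and state that it assumes missing at random.
- Add an analysis for patients whose stroke status remains unknown after the record and register checks: either best/worst-case bounds by arm, or a delta-adjusted tipping-point analysis that varies the odds of stroke among them separately in each arm. Report how many such patients there are in each arm.
- Do not impute 90-day blood pressure, cholesterol or EQ-5D for patients who died as if they were alive. Show survivors' values with the deaths alongside.

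The cost is a sentence or two, a few extra model runs and a wider reported range. The pilot is a cheap time to do it, since it is already meant to establish the follow-up rate and the feasibility of the outcomes for the main trial.
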